#### Comparison of microbiota between the 2 treatment groups

4.8.6

These comparisons will use the same tests as in the previous paragraph, except tests will not be paired.

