**Methods::**

The study is a case-controlled observational trial. Forty NSCLC patients will be divided into 2 groups depending on their anamnesis: Pchir, patients eligible for surgery, or Pct-chir, patients eligible for neoadjuvant chemotherapy plus surgery. Composition of the UAs (saliva), gut (faeces), and lung microbiota (from broncho-alveolar lavage fluid (BALF) and 3 lung pieces: “healthy” tissue distal to tumour, peritumoural tissue and tumour itself) will be analysed in both groups. Immune properties will be evaluated on the local (evaluation of the tumour immune cell infiltrate, tumour classification and properties, immune cell phenotyping in BALF; human neutrophil protein (HNP) 1–3, β-defensin 2, and calprotectin in faeces) and systemic level (blood cytokine and immune cell profile). Short-chain fatty acids (SCFAs) (major products of bacterial fermentation with an effect on immune system) will be dosed in faecal samples. Other factors such as nutrition and smoking status will be recorded for each patient. We hypothesise that smoking status and tumour type/grade will be major factors influencing both microbiota and immune/inflammatory profile of all sampling sites. Furthermore, due to non-selectivity, the same effect is expected from chemotherapy.

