A demanded control group for the study was not authorised by the Ethics Committee, due to the invasiveness or evident inability to realise certain sampling steps (bronchoscopy, lung tissue sampling). Therefore, the focus will be on characterisation of the site-related microbiota and its connection to local and systemic immunity in NSCLC respective of the treatment group (Pchir or Pct-chir). Likewise, the question is whether there is an initial difference between group Pchir and group Pct-chir (before CT1), and what its nature is. Equally, how does chemotherapy modify group Pct-chir, and whether it becomes more alike or different from group Pchir regarding its different properties (microbial taxa ratios, inflammatory properties) when followed in time (from CT1 to surgery). Furthermore, obtained results considering microbiota composition and abundance, where possible, will address similar studies^[13–16]^ only in a descriptive matter and the same will be done with immune parameters.^[17–21]^

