#### General information

4.8.1

This study is exploratory and main outcomes address the description of microbiota characteristics in lung cancer patients. Three microbiota are concerned (gut, lung, and saliva) and data are collected at different times in patients treated by neoadjuvant chemotherapy (group Pct-chir). For other patients (group Pchir), different microbiota are sampled at only 1 time point, at surgery.

In patients treated by chemotherapy, analysis of variations of microbiota induced by chemotherapy will be possible by evaluation of changes in proportions over time. On the other hand, the analysis of microbiota with/without previous chemotherapy will only be descriptive, as the design is not compatible with a non-biased comparison of both groups.

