#### Comparison of microbiota before/after chemotherapy

4.8.5

This comparison will be performed for each site-specific microbiota. Proportions of main phyla will be compared using ANOVA (mixed model) to check if an independent chemo-effect can be objectivised, adjusting on patients and phyla (without FDR correction).

Comparisons of taxonomic levels below phylum before/after chemotherapy will be performed on relevant components with an FDR correction. These comparisons will be performed on both alpha and beta diversity. Univariate paired parametric or non-parametric tests (Student *t* test, Mann–Whitney *U* test, etc.) will be used here.

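### Section 4.8.1 limits the with/without-chemotherapy comparison to description because it is biased, but section 4.8.6 orders significance tests between the same two groups; at surgery the two cannot both be followed.

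*Protocol article*

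**What the plan says.** Section 4.8.1 (General information) calls the study exploratory and treats two questions differently. Change over time within the chemotherapy group (Pct-chir) may be analysed. For the other question it says that "the analysis of microbiota with/without previous chemotherapy will only be descriptive, as the design is not compatible with a non-biased comparison of both groups".

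Section 4.8.6 (Comparison of microbiota between the 2 treatment groups) consists of one sentence: "These comparisons will use the same tests as in the previous paragraph, except tests will not be paired". The preceding section, 4.8.5, holds two procedures:

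- for the main phyla, an ANOVA (mixed model), "adjusting on patients and phyla (without FDR correction";
- below phylum, comparisons that "will be performed on relevant components with an FDR correction", using "Univariate paired parametric or non-parametric tests" such as Student's t or Mann–Whitney.

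Section 4.8.9 makes all tests two-sided at 0.05, after FDR correction where needed, and exempts none.

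Section 2.5 (Trial design and timeline) raises two between-group questions. One is "whether there is an initial difference between group Pchir and group Pct-chir (before CT1), and what its nature is". The other is whether Pct-chir moves closer to or further from the surgery-only group (Pchir) between CT1 and surgery. On what may drive the outcomes, the Abstract states: "We hypothesise that smoking status and tumour type/grade will be major factors influencing both microbiota and immune/inflammatory profile of all sampling sites".

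**The concern.** One section rules out inference on a contrast because it is biased, and another prescribes hypothesis tests for what appears to be the same contrast. An analyst cannot comply with both at surgery.

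Group membership is not randomised: section 2.3 assigns patients by diagnosis, and section 5.3 suggests that the tumour properties leading to chemotherapy may separate the two patient profiles. A significant difference at surgery could therefore reflect chemotherapy, the reason chemotherapy was given, or both. If 4.8.6 is followed, the report will contain P values that can be read as chemotherapy effects, from a comparison that the plan itself says cannot support them. Lung microbiota is part of the primary outcome in section 2.2, so this is not confined to a marginal sample type.

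**Working it through.** **Step 1. Which tests pass from 4.8.5 into 4.8.6?** With pairing removed, they are the phylum-level ANOVA without FDR correction and unpaired univariate tests with FDR correction below phylum. The only adjustment named is for patients and phyla. Each patient belongs to one group, so a patient term cannot remove a difference between groups that existed before treatment. Univariate tests carry no covariates.

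**Step 2. Which contrasts are possible at each site?** From the sampling schedule in sections 2.5 and 3.5:

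| Sample | Pchir at surgery v Pct-chir before CT1 | Pchir v Pct-chir at surgery |
|---|---|---|
| Saliva, faeces | available | available |
| BALF | Pct-chir only if bronchoscopy was prescribed, and by a different sampling technique from Pchir | available |
| Distal, peritumoural and tumour tissue | not available | available |

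In the first column no patient has yet had the study chemotherapy. In the second, treatment group and previous chemotherapy coincide. That column is the contrast that 4.8.1 restricts to description, and for lung tissue there is no other.

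**Step 3. Does 4.8.6 choose between them?** No. It names no time point and does not describe its tests as descriptive. Section 4.8.9 attaches a significance threshold to them.

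**Step 4. Does the sample size depend on the between-group test?** No. Section 4.8.2 bases n = 20 on the before/after change in faecal *Firmicutes* (a fall of about 30%) and sets the surgery-only group at 20 for balance. It states no SD and no power, so n = 20 cannot be reproduced, and this point does not need it.

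**Step 5. What could confounding do to one test? Illustration only.** Inputs: 20 per group (section 4.8.2), two-sided 0.05 (section 4.8.9), no true chemotherapy effect. The confounding bias b, in SD units, is assumed, because the documents give no figure for it.

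For an unpaired t test with 38 degrees of freedom, the noncentrality is b / √(2/20) = b × √10, and the two-sided critical value is 2.024.

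| Assumed b | Noncentrality | Rejection rate |
|---|---|---|
| 0 | 0 | 5.0% |
| 0.2 | 0.2 × 3.162 = 0.632 | 9.5% |
| 0.4 | 0.4 × 3.162 = 1.265 | 23.4% |

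These rates are per test. FDR correction below phylum controls chance findings among many tests. It does not remove a systematic difference between the groups.

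**The case against.** The strongest defence is one of scope. Section 4.8.1 restricts the analysis with and without previous chemotherapy, and before CT1 neither group has had the study chemotherapy. Sections 2.5 and 5.3 ask about exactly that initial difference, so 4.8.6 may have been written for it. This stands for the pre-CT1 contrast. It does not rescue the contrast at surgery, because 4.8.6 does not limit itself to baseline and lung tissue exists only at surgery.

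A second defence is that the study is exploratory, its primary outcome is characterisation, 4.8.1 already warns of bias, and time points or covariates for each test may sit in a fuller plan that is not shown. This lowers the severity, and the absence of such detail is not criticised here. It does not reconcile two statements that the article itself makes.

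A reader might also infer more than the documents support:

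- **That the tests are wholly unadjusted.** FDR correction applies below phylum, and the phylum model adjusts for patients and phyla. What is not stated is adjustment for confounders.
- **That 24 uncorrected phylum tests are planned (4 phyla × 6 sample types), with a 71% chance of at least one false positive.** Section 4.8.5 makes phylum a term in a model fitted for each site. One test per sample type gives 6 tests and 1 − 0.95^6 = 26%. Even that assumes independence, which six sample types from the same patients do not have.
- **That tumour characteristics differ between the groups by design.** Section 5.3 offers this only as a hypothesis, and nothing shown says that smoking or histology differs by group.

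**Conclusion.** The concern holds in a limited form. For the groups at surgery, 4.8.1 and 4.8.6 contradict each other: the plan calls for description only and also for tests at 0.05. For Pchir versus Pct-chir before CT1, the text can be read as consistent, and 4.8.6 may serve that question.

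The contradiction rests on the wording alone. The rates of 9.5% and 23% depend on assumed biases of 0.2 and 0.4 SD and show how confounding would act; they do not estimate it in this trial. That readers would take the P values as treatment effects is a risk, not something the documents establish.

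This should be fixed, but it does not endanger the study: the main outcomes are descriptive, and n = 20 rests on the before/after change.

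**What to change.** Rewrite 4.8.6 so that it agrees with 4.8.1:

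1. **Groups at surgery, all sample types:** report estimates of the group differences with 95% confidence intervals, without significance tests and without attributing differences to chemotherapy. The question in section 2.5 of whether Pct-chir comes to resemble Pchir by surgery is then answered descriptively.
2. **Pchir versus Pct-chir before CT1:** state that any tests in 4.8.6 apply only to this contrast, in saliva and faeces, and that results are reported as a difference between two patient populations and not as a treatment effect.
3. **Optional:** a sensitivity analysis of the pre-CT1 contrast adjusted for smoking status and tumour type, where numbers permit. With 20 per group it may not be feasible, and tumour type may be part of the population difference that section 2.5 sets out to describe. Smoking status is already recorded (section 2.5), as are stage and histology (section 5.3).

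The cost is a few sentences and fewer P values to report. No sample size, visit or sample changes.

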#### Relationship between inflammatory status and microbiota

4.8.7

Several cytokines will be measured in blood samples. Each result will consist in a concentration of cytokine. The relationship between microbiota and inflammation will be tested using Pearson (or Spearman rank) correlation coefficient, using FDR correction.

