
Therefore, to help to elucidate this new and extremely interesting field, we have decided to conduct a case-control observational study in patients with NSCLC. The study will include 2 groups of patients: 1st group Pchir, with patients eligible for treatment by surgery, and 2nd group Pct-chir, with patients eligible for a combined treatment consisting of neoadjuvant platinum-based chemotherapy followed by surgery.

The objectives of this study are:

(i)to characterise the gut, lung and upper airway microbiota in these patients;(ii)to evaluate the homogeneity/heterogeneity between different microbiota within the same subject/group of patients;(iii)to evaluate the impact of the microbiota composition on immune and inflammatory status of the patient (evaluated in the gut, blood, lung);(iv)to evaluate the effect of chemotherapy on the site-specific microbiota (UAs, lung, gut).

While group Pchir will have only 1 time point for sample collection, group Pct-chir will have multiple time points. The latter will enable follow-up on changes in microbiota and immune markers relative to the treatment progression.

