### Study outcomes

2.2

As its primary outcome, this study will characterise the lung and UAs microbiota in 2 groups of 20 patients with NSCLC. Group Pchir will include patients eligible for surgery without chemotherapy. Group Pct-chir will include patients eligible for surgery after platinum-based chemotherapy. The UAs microbiota will be evaluated from saliva, while lung microbiota will be evaluated from 3 lung explants: “healthy” lung tissue, tumour and peritumoural tissue; and broncho-alveolar lavage fluid (BALF) from the tumour's proximity (same lobe). Following bacterial DNA extraction, microbiota will be analysed by qPCR and 16S ribosomal rRNA gene sequencing using the Illumina MiSeq platform.

Secondary outcomes of this study are set as follows:

i)to study the effect of neoadjuvant chemotherapy on microbiota by evaluating:a.the variation of the proportion of the phylum *Firmicutes* (as the phylum is highly represented in all of the different types of samples considered in this study),^[4]^b.the variation of the proportion of the bacterial genera per phylum in different types of samples (faeces, saliva, BALF, lung tissue/peritumoural tissue/tumour),c.the concordance of genera between sample locations (e.g. saliva vs. BALF, healthy lung tissue vs. peritumoural tissue vs. tumour);by qPCR and 16S rRNA gene sequencing;ii)to study the homogeneity/heterogeneity between lung, upper airways and gut microbiota for each and between both groups (evaluated by 16S rRNA gene sequencing and qPCR) and between different time points (group Pct-chir),iii)to evaluate immune/inflammatory status:a.in the gut: by dosing β-defensin 2, human neutrophil peptides HNP1-3, calprotectin (ELISA) and SCFAs (gas liquid chromatography)b.in plasma: by dosing plasmatic cytokines (Luminex), C-reactive protein (CRP) (ELISA) and immune cell phenotyping (flow cytometry)c.in the lung: by immune cell phenotyping (flow cytometry) and characterisation of immune infiltrate in lung tumour biopsies obtained during the operation (by immunohistochemistry).

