#### Tumoural immune infiltration

4.8.8

Immune reaction will be described by percentage by lymphocyte type. These proportions will be compared to corresponding microbiota characteristics: for example lung microbiota and lung tumour. Statistical association between these parameters will be tested as in the previous paragraph.

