As mentioned, intestinal microbiota has both local and systemic influence on its host. According to the gut-lung axis theory,^[4]^ bacteria or their products might have systemic effects, and therefore, have an effect on the lung microbial composition and immune response. For this reason, faecal microbiota will be characterised, as well as faecal SCFAs concentrations (known products of bacterial fermentation and immune modulators/protectors of the intestinal barrier).^[74]^ The SCFAs might be potential mediators of the gut's “long-distance” influence by direct effect on the target site or indirectly via gut/circulating immune system stimulation. As intestinal microbiota is shown to adapt very quickly to the changes in nutrition, as well as its influence on SCFAs concentrations,^[22,75]^ nutritional records before each faecal sampling will be taken into account. We will not only determine the composition of faecal microbiota, but also its “quality” and influence on intestinal health by dosage of bacteriocins (HNP1-3, β-defensin 2), and calprotectin as inflammatory marker.^[76]^ Broad-spectrum cytokine profiling and immune cell phenotyping in the blood will be used to evaluate systemic immune status. This holds particular importance as connection to circulating IL-6 and IL-8 was previously reported in lung cancer,^[76,77]^ but also to intestinal SCFA concentrations.^[78]^

As explained, group Pct-chir will enable follow-up on multi-site microbiota and immune status during different treatment phases (Fig. 1). Since the biggest problem of chemotherapy, despite its efficacy against tumour cells, is its non-selectivity (effecting epithelial layers and mucosae),^[79–81]^ we expect to see changes in all 3 types of microbiota—salivary, faecal, and lung, as all are closely related to epithelial and mucosal layers. Similarly, immune characteristics should be altered following the chemotherapy and above-mentioned changes in microbiota (but also vice versa—the affected immune system will change its interaction with microbiota, thus modifying it). Finally, we could hypothesise that different initial properties of the tumour (why the patient is prescribed chemotherapy or not in the 1st place) might divide 2 patient profiles (Pchir vs. Pct-chir 1st time point) regarding both multi-site microbial and immune/inflammatory characteristics.

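### Sections 4.8.7 and 4.8.8 test microbiota-immune associations with an unadjusted correlation, although the protocol expects chemotherapy, smoking and tumour type to shift both variables

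*Protocol article*

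**What the plan says.** Section 4.8.7 fixes the test: "The relationship between microbiota and inflammation will be tested using Pearson (or Spearman rank) correlation coefficient, using FDR correction". It does not say whether Pchir and Pct-chir are combined, which time point is used, or whether anything is adjusted for. Section 4.8.8, on the tumour infiltrate, adds: "Statistical association between these parameters will be tested as in the previous paragraph". Section 4.8.9 sets two-sided testing at 0.05, after FDR correction where needed.

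These tests serve objective (iii) in the Introduction, which is "to evaluate the impact of the microbiota composition on immune and inflammatory status of the patient".

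The Methods part of the abstract says: "We hypothesise that smoking status and tumour type/grade will be major factors influencing both microbiota and immune/inflammatory profile of all sampling sites". It adds that "the same effect is expected from chemotherapy". Section 5.3 repeats the immune side of this: "Similarly, immune characteristics should be altered following the chemotherapy and above-mentioned changes in microbiota".

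Section 2.5 records smoking status and history at Visit 1, and section 5.3 says that each tumour is characterised by stage and histology. The covariates are therefore in the data.

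**The concern.** By the protocol's own hypothesis, chemotherapy, smoking and tumour type are common causes of the two variables being correlated. A plain correlation across patients who differ on these factors contains the shared shift as well as any direct link, and cannot separate them. Section 4.8.1 says that the design does not support an unbiased comparison of the two groups. A correlation pooled over the groups brings that same between-group contrast back in.

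FDR correction limits the share of chance findings among those declared, provided each p-value is valid under its null hypothesis. Under confounding the p-values are not valid for the question asked, so the correction does not help.

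Objective (iii) speaks of impact, and section 5.4 says that the study will concentrate on relational questions because there is no healthy control group. A confounded association could therefore be reported as a link between microbiota and immunity.

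**Working it through.** **Inputs from the document.** "this study will characterise the lung and UAs microbiota in 2 groups of 20 patients with NSCLC" (section 2.2), so n = 20 + 20. Two-sided 0.05 (section 4.8.9). Pearson or Spearman without covariates (section 4.8.7). The plan gives no figure for this test that could be reproduced; its sample-size statement (section 4.8.2) concerns the fall in *Firmicutes*.

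**Assumptions, because the document gives no values.** Each factor shifts both variables by the same d, from 0.5 to 1.5 SD. The variables are normal and independent once the factors are known. Half the patients had chemotherapy before sampling. 80% are ever-smokers, spread equally over the groups.

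**Step 1: correlation induced by one shared factor.** With a proportion p exposed,

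r = p(1-p)d² / (1 + p(1-p)d²).

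For chemotherapy p = 0.5, so p(1-p) = 0.25:
- d = 0.5: 0.0625/1.0625 = 0.06
- d = 0.8: 0.16/1.16 = 0.14
- d = 1.0: 0.25/1.25 = 0.20
- d = 1.5: 0.5625/1.5625 = 0.36

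**Step 2: false-positive rates.** Simulation with no direct link, all 40 patients pooled, one sample each, 20,000 runs per setting:

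| Shift d (SD) | Chemotherapy only, Pearson | Chemotherapy only, Spearman | Chemotherapy only, Pearson adjusted for group | Chemotherapy and smoking, Pearson unadjusted | Both, adjusted for group only | Both, adjusted for both |
|---|---|---|---|---|---|---|
| 0.5 | 7% | 6% | 5% | 9% | 6% | 5% |
| 0.8 | 14% | 14% | 5% | 26% | 9% | 5% |
| 1.0 | 24% | 24% | 5% | 48% | 14% | 5% |
| 1.5 | 68% | 71% | 5% | 94% | 40% | 5% |

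Adjusting for group alone is enough only when group is the only shared factor. If smoking acts too, it has to be in the adjustment.

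**Step 3: FDR.** Take 60 null pairs (the 4 phyla of section 4.8.4 times an assumed 15 cytokines), both factors acting, Benjamini-Hochberg at 0.05, 2,000 runs. The chance of at least one declared pair is 15%, 68%, 97% and 100% at d = 0.5, 0.8, 1.0 and 1.5. On average 0.2, 3, 16 and 56 of the 60 are declared. After adjustment for both factors the chance of any declared pair is 4.5-5.6%.

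**Step 4: correlation within one group of 20.** The between-group chemotherapy part is gone. Smoking alone then gives 5%, 7%, 9% and 21% (Pearson) or 5%, 6%, 8% and 17% (Spearman) at the same four shifts.

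**Step 5: stacking CT1 and surgery samples (section 4.8.7 only).** Pct-chir has blood at both times, so stacking gives 20 + 2 × 20 = 60 observations from 40 patients. With an assumed within-patient correlation of 0.5 in each variable and no shift, the variance of r grows by about (60 + 2 × 20 × 0.5²)/60 = 70/60 = 1.17. The normal approximation then gives a rejection rate near 7%; simulation gave 6.6%. For Pct-chir alone the factor is (40 + 10)/40 = 1.25, or about 8%. Lost independence is thus a small effect by itself. With a chemotherapy shift added, the 60-observation version rejects about 17%, 30% and 79% at 0.8, 1.0 and 1.5 SD, and most of that comes from the shift.

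**The case against.** The best reply is that pooling is not written down. Section 2.5 frames the link to immunity by treatment group, section 4.8.1 warns against comparing the groups, and section 2.5 allows BALF time points to be characterised separately. With by-group correlation at a single time point, chemotherapy causes no inflation. This stands as far as it goes. However, section 4.8.7 does not carry the by-group intention into the test, smoking would still be uncontrolled, and nothing there rules out stacking CT1 and surgery samples within Pct-chir.

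A second reply is that an article condenses a longer protocol, that the study is exploratory, and that section 4.8.9 leaves room for complementary analyses. But section 4.8 is headed as the analysis plan, names the test and sets a significance level. Section 4.8.5 does specify adjustment where it is wanted. The exploratory label lowers the weight of the point without answering it.

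Some stronger readings go too far:
- A reader might infer that spurious associations will certainly arise. The documents give no shift size, and at 0.5 SD the inflation is slight.
- A reader might infer that the study's main result is at risk. The primary outcome is characterisation of the lung and upper-airway microbiota; immune status is secondary outcome iii.
- A reader might take non-independence as a defect of both sections. It depends on stacking, and it does not reach section 4.8.8, because tumour tissue is taken only at surgery.
- A reader might conclude that Pearson must be ruled out as such. Nothing here shows that; Spearman is already allowed and is confounded in the same way.

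**Conclusion.** The point holds in conditional form. The test as stated is unadjusted, and the protocol itself names factors expected to move both variables. If the groups are pooled and the hypothesis is right, false associations can arise that FDR correction leaves in place. With chemotherapy as the only shared factor the error rate is 6-7% at 0.5 SD and about 70% at 1.5 SD; with smoking as well it is 9% to 94% over the same range. These figures rest on the assumed shift, its equal size in both variables and the assumed 80% share of smokers. The direction of the problem follows from the protocol's text; its size does not. By-group analysis would be a partial remedy. The point is worth correcting before the correlations are run.

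**What to change.** In sections 4.8.7 and 4.8.8, specify a partial Spearman correlation on the surgery sample, one per patient, adjusted for treatment group and smoking status. Add tumour type as a sensitivity analysis where numbers allow. In section 4.8.7, analyse within-patient changes from CT1 to surgery separately in Pct-chir instead of stacking the two time points. Keep the FDR correction.

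Chemotherapy precedes the surgery samples, so adjusting for treatment group removes the shift it causes in both variables without removing a microbiota-immune link that exists within groups.

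The cost is 2-3 degrees of freedom out of 40 patients and slightly more analysis work. No new data are needed. With 20 to 40 patients only a few covariates can be carried, so the list should stay this short.

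If by-group correlation is what is intended, section 4.8.7 should say so, name the time point and still adjust for smoking.
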